#### Metabolomic study

All the metabolomic analyses and data processing will be carried out with methods previously described [24–26].

##### Sample preparation

The samples will be prepared using the automated MicroLab STARR (Hamilton Company, Salt Lake City, UT, USA) robot system. For quality control (QC) purposes, a recovery standard will be added to 100 L of the serum samples before the first step in the extraction process. The proteins will be precipitated with methanol by vigorously shaking for 2 min. Next, the samples will be centrifuged to remove the proteins, dissociate the small molecules bound to the proteins or trapped in the precipitated protein matrix, and to recover chemically diverse metabolites (Glen Mills GenoGrinder 2000, Lebanon, USA). Then, the samples will be placed on a TurboVapR (Zymark, California, USA) to remove the organic solvent. For liquid chromatography (LC) analysis, the samples will be stored overnight in nitrogen before preparation. For gas chromatography (GC) analysis, each sample will be dried overnight under vacuum before preparation [24].

##### Quality controls

Several types of control experiments will be performed in parallel with the experimental samples. A pooled matrix sample, generated by taking a small volume of each experimental sample, will serve as a technical replicate throughout the extracted data set. Water aliquots will serve as process blanks. Moreover, a cocktail of QC standards carefully chosen not to interfere with the measurement of endogenous compounds will be spiked into every analyzed sample. This will allow instrument performance monitoring and aid in the chromatographic alignment. The instrument variability will be determined by calculating the median relative standard deviation (RSD) for the standards that will be added to each sample before injection into the mass spectrometers (MS). The entire process variability will be determined by calculating the median RSD for all the endogenous metabolites (i.e., non-instrument standards) present in 100% of the pooled matrix samples. The experimental samples will be randomized across the platform run with the QC samples spaced every 5 or 10 injections to verify overall assay performance [24]. The internal standards will be used to measure the instrument variability and will have a median RSD of 3%. Additionally, the total process variability will be 8%.

##### Ultra-performance liquid chromatography-tandem mass spectrometry

The liquid chromatography/mass spectrometry (LC/MS) portion of the platform to be used will employ a Waters ACQUITY ultra performance liquid chromatography (UPLC), a Thermo Scientific Q-Exactive high-resolution/accurate MS interfaced with a heated electrospray ionization (HESI-II) source, and an Orbitrap mass analyzer operated at a 35,000 mass resolution. The sample extract will be dried and reconstituted in acidic or basic LC-compatible solvents, each of which will contain eight or more injected QC standards at fixed concentrations to ensure injection and chromatographic consistency. One aliquot will be analyzed using acidic, positive ion-optimized conditions, and another will be performed using basic, negative ion optimized conditions in two independent injections using separate dedicated columns (Waters UPLC BEH C18–2.1 × 100 mm, 1.7 m). The extracts reconstituted in acidic conditions will be gradient-eluted from a C18 column using water and methanol containing 0.1% formic acid. A second aliquot, from the basic extract, will be similarly eluted from a C18 column using methanol, water, and 6.5 mM ammonium bicarbonate. A third aliquot will be analyzed via negative ionization following elution from a hydrophilic interaction chromatography column (Waters UPLC BEH Amide 2.1 × 150 mm, 1.7 m) using a gradient consisting of water and acetonitrile with 10 mM ammonium formate [24].

##### Gas chromatography-mass spectrometry

The samples destined for analysis by GC-MS will be dried under a vacuum for a minimum of 18 h before being derivatized under dried nitrogen with bistrimethylsilyltrifluoroacetamide. The derivatized samples will be separated on a 5% diphenyl/95% dimethyl polysiloxane fused silica column (20 m × 0.18 mm id; 0.18 m film thickness) with helium as the carrier gas and a temperature ramp from 60C to 340C over a 17.5-min period. The samples will be analyzed on a Thermo-Finnigan Trace DSQ fast-scanning single-quadrupole MS using electron impact ionization (EI) operated at unit mass resolving power. The scan range will be 50–750 m/z [24].

##### Data extraction and compound identification

The raw data will be extracted, and the peaks will be aligned and identified. QCs will be processed using specific hardware and software [25]. The peaks will be quantified using the area-under-the-curve (AUC) calculation. The compounds will be identified comparing the data to library entries of purified standards or recurrent unknown entities. The biochemical identifications will be based on three criteria: the retention index (RI) within a narrow RI window of the proposed identification, an accurate mass match to the library ±0.005 amu, and the MS/MS forward and reverse scores between the experimental data and authentic standards. The MS/MS scores will be based on a comparison of the ions present in the experimental spectrum with the ions present in the library spectrum. Although there may be similarities between these molecules based on one of these factors, the use of all three data points can be utilized to distinguish and differentiate the biochemicals with precision.

#### Evaluation of DNA damage by determination of phosphorylated histone 2AX (P-H2AX)

Breast biopsies will be homogenized and seeded onto specific culture media to isolate bacterial colonies which later on will be evaluated based on their ability to generate nicks in the DNA of HeLa cells using the P-H2AX marker [27]. For this purpose, after colony isolation an under both aerobic and anaerobic conditions, bacterial species will be identified by PCR amplification of 16S rRNA gene. Then bacterial candidates will be used to infect HeLa cells in 24 well-dishes for 24 h. Cells will be fixed and subjected to immunofluorescence using an anti-phosphorylated histone 2AX (P-H2AX, rabbit anti-phosphohistone-2AX MAb; Cell Signaling Technologies, ref. 9718). Fluorescence intensity will be measured and the percentage of P-H2AX positive cells will be calculated.

### Quantitation of the exposure to EDCs in urine samples

Analysis of non-persistent EDCs will be carried out by dispersive liquid–liquid microextraction (DLLME) and ultra-high performance liquid chromatography with tandem mass spectrometry detection (UHPLC-MS/MS) as previously described with minor modifications [28, 29]. Briefly, urine samples will be thawed completely at room temperature, centrifuge at 2600 x g for 10 min to sediment particulate matter and 0.75 mL will be taken to carry out the analysis. In order to determine total EDCs amount (free plus conjugated) in urine, each sample will be spiked with 50 μL of enzyme solution (β-glucuronidase/sulfatase) and incubated at 37 °C for 24 h. The treated urine will be placed in a 15 mL screw-cap glass tube and spiked with 30 μL of the surrogate standard solution (1.25 mg/L of BPA-d_16_). Urine will be diluted to 10.0 mL with 5% NaCl aqueous solution (w/v) and the pH will be adjusted to 2.0. Next, 0.75 mL of acetone and 0.75 mL of trichloromethane will be mixed and injected rapidly into the aqueous sample with a syringe. After manual shaking, centrifugation and evaporation of the extract, the residue will be dissolved with 100 μL of a mixture consisting of water (0.1% ammonia)/acetonitrile (0.1% ammonia), 70:30 (v/v), and finally 10 μL will be injected in the LC system. Urinary creatinine concentration (mg/dL) will be determined using an automated colorimetric determination, in the same urine samples in which environmental chemical will be assessed. Because of the relatively constant excretion rate of creatinine into the urine (which makes urinary creatinine concentration inversely proportional to urine flow rate), creatinine adjustment is widely used to normalize analyte concentrations in spot samples for environmental exposure monitoring [30].

Bisphenols [bisphenol A (BPA), bisphenol S (BPS) and bisphenol F (BPF)], parabens [(metylparaben (MeP), ethylparaben (EtP) propylparaben (PrP) and butylparaben (BuP)], benzophenones [(UV filters: benzophenone-1 (BP-1), benzophenone-3 (BP-3) and 4-hidroxybenzophenone (4-OH-BP)] will be determined. Final concentrations will be adjusted for urinary creatinine levels (mg/dl), to account for both urine dilution and body composition, as previously reported [31, 32].

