### Study subjects

#### Inclusion and exclusion criteria

In this ongoing case-control study, already registered in ClinicalTrials.gov (Identifier NCT03885648), women’s age will range 25–70 years. Cases will be defined as women diagnosed and surgically intervened of incident breast cancer, stages I and II. Controls will be women surgically intervened of breast augmentation or reduction. Women with antecedents of cancer or advanced tumor stage (metastasis), or who have received antibiotic treatment within a period of 3 months prior to recruitment, or any neoadjuvant therapy, will be excluded of the study. Women with oncological, gynecological or endocrine antecedents and those who have received antibiotic treatment within a period of 3 months prior to recruitment will be also excluded. Controls will be matched to cases by age (± 2 years), category of body mass index and hospital of recruitment.

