### Quantitation of urinary concentrations of the parent estrogens and estrogen metabolites

Concentrations of estrone, estradiol and 13 estrogen metabolites [2-hydroxylated estrogen metabolites (2-hydroxyestrone, 2-methoxyestrone, 2-hydroxyestradiol, 2-methoxyestradiol, and 2-hydroxyestrone-3-methyl ether); 4-hydroxylated estrogen metabolites (4-hydroxyestrone, 4-methoxyestrone, and 4-methoxyestradiol); and 16-hydroxylated estrogen metabolites (16α-hydroxyestrone, estriol, 17-epiestriol, 16-ketoestradiol, and 16-epiestriol)] will be determined in fasting spot urine samples, adjusting for urinary creatinine levels (mg/dL). The quantitation of urinary estrogens will be assessed by gas chromatography tandem mass spectrometry using a triple quadrupole analyzer as previously described with minor modifications [33, 34]. Briefly, one mL of urine with 25 μL of internal standards solution will be extracted using C18 SPE cartridge (Sep-Pack C18) previously conditioned with 4 mL of methanol and 4 mL of water. After loading the urine sample, the cartridge will be washed with 4 mL of water. The treated urine will then be evaporated. Three mL of acetate buffer 0.1 M (pH 4.5) and 3 μL of β-glucuronidase will be added to the treated urine after being evaporated, and the mixture will be incubated for 3 h at 55 °C. After cooling to room temperature, pH will be increased to approximately 9.5. Then, samples will be extracted with 6 mL of tert-butyl methyl ether by shaking in a rocking mixer and centrifuged. Finally, the organic layer will be evaporated to dryness under a stream of nitrogen. Two μL of the derivatized extract will be injected in split mode into the GC-MS/MS system. All hormone assessments will be carried out simultaneously to reduce intralaboratory variation.

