Random forest (RF) is a supervised classification technique based on an ensemble of decision trees [35] with several advantages. It makes no parametric assumptions, and variable selection is not needed. It does not overfit, and it is invariant to transformation. In RF analysis, it is not necessary to cross-validate or do a separate test set to obtain an unbiased estimate of the test set error. A “variable importance” measure will be computed to determine which variables (metabolites) make the largest contribution to the classification. The mean decrease in accuracy (MDA) will be used as this metric and will be determined by randomly permuting a variable, running the observed values through the trees, and then reassessing the prediction accuracy. If a variable were not significant, then this procedure will have little change in the accuracy of the class prediction (permuting random noise will give random noise). By contrast, if a variable is relevant for the classification, the prediction accuracy will drop after such a permutation, which will be recorded as the MDA. Thus, the RF analysis provides an “importance” rank ordering for biochemicals [35].

Participants will be grouped into tertiles of urinary EDC levels based on their distributions among the controls. Odds ratios and 95% confidence intervals (CIs) for breast cancer comparing the second and third tertiles with the first tertile will be estimated using logistic regression models. Further, associations of participant characteristics with urinary EDC levels, estrogens and estrogen metabolites and fecal microbiome measures will be evaluated by using general linear models and testing either for differences across categories or for trends across categories. Linear regression models will also be used to evaluate associations of each steroid measure with measures of the diversity of the fecal microbiome, abundance and with taxonomic groups at phylum and family levels, adjusting by covariates.

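### Creatinine adjustment is said to account for body composition; a ratio would instead carry age and body size into the adjusted EDC and estrogen levels and can create false associations with participant characteristics

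*Protocol article*

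**What the plan says.** All references are to the protocol article.

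- **Reason for adjusting (Quantitation of the exposure to EDCs in urine samples).** The argument opens "Because of the relatively constant excretion rate of creatinine into the urine" and goes on to say that "creatinine adjustment is widely used to normalize analyte concentrations in spot samples for environmental exposure monitoring".
- **Claimed property (same section).** "Final concentrations will be adjusted for urinary creatinine levels (mg/dl), to account for both urine dilution and body composition". No formula is given; the sentence refers to earlier reports for the method.
- **Estrogens (Quantitation of urinary concentrations of the parent estrogens and estrogen metabolites).** Estrone, estradiol and 13 metabolites "will be determined in fasting spot urine samples, adjusting for urinary creatinine levels (mg/dL"). Body composition is not given as a reason here.
- **Use of the levels (Statistical analysis).** General linear models will examine "associations of participant characteristics with urinary EDC levels, estrogens and estrogen metabolites". EDC levels are also cut into tertiles at the control distribution, with odds ratios "comparing the second and third tertiles with the first tertile will be estimated using logistic regression models".
- **Design (Inclusion and exclusion criteria).** Women are aged 25 to 70. "Controls will be matched to cases by age (± 2 years), category of body mass index and hospital of recruitment".
- **Recorded variables (Anthropometric and sociodemographic information).** Age, race, weight and height are recorded. Muscle mass is not listed.

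**The concern.** The two reasons given for the adjustment do not fit together. Suppose creatinine output is the same in all women. It then corrects for dilution but carries no information on body composition, so it cannot account for it. Suppose instead that it is constant within a woman but differs between women with muscle mass and age. Dividing by it then corrects for dilution and also multiplies each level by the inverse of that woman's creatinine output. Body composition and age are put into the adjusted level, not taken out.

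The analysis most exposed is the set of participant-characteristic models. Age and weight are among the recorded characteristics, and a driver of creatinine would be tested against a variable with creatinine in its denominator. Older or less muscular women could appear more exposed, or appear to have higher estrogen levels, when they do not. Case-control matching gives no protection here, because it balances the two groups and leaves the age range within the sample intact.

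**Working it through.** The plan gives no figure to reproduce. The checks below rest on assumptions about creatinine that the document does not supply, shown as ranges.

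**1. Age artefact in a simple ratio.** Inputs: ages 25 to 70, so 45 years (document); creatinine output falling 0.5% or 1% per year (assumption); true exposure unrelated to age.
- At 0.5% per year: 1 / 0.995^45 = 1.25, a rise of 25%.
- At 1% per year: 1 / 0.99^45 = 1.57, a rise of 57%.

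On the log scale these declines are 10 × ln(0.995) = −0.050 and 10 × ln(0.99) = −0.101 per decade.

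**2. False-positive rate in the age model.** Simulation with 100 cases and 100 controls (document) and age matched within 2 years (document), 600 runs per setting. True EDC excretion was independent of age, lean mass and case status. Assumptions: SD of log excretion 0.7 to 1.3, SD of log urine flow 0.6, SD of log lean mass 0.15, SD of other log creatinine noise 0.1. Log(EDC/creatinine) was regressed on age at the 5% level.

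| Change in log creatinine per decade | False-positive rate |
|---|---|
| 0 | 4–6% |
| −0.05 | 10–25% |
| −0.10 | 27–69% |
| −0.15 | 51–94% |

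The false slope on age is, apart from simulation error, the creatinine decline with its sign reversed. Using log creatinine as a covariate in place of the ratio, with nothing else in the model to represent what drives creatinine, still gave 22–58% at −0.10 per decade.

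**3. EDC odds ratios under the stated matching.** In the same simulations, with no residual lean-mass difference between cases and controls, the third-versus-first tertile odds ratio (true value 1) was 0.94 to 0.99 at every age slope, with 4–6% false positives. With no link between creatinine and age at all it was 0.96 to 0.97. Age therefore does not move the odds ratios once it is matched.

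**4. EDC odds ratios if a case-control difference in creatinine output remained.** Assume log adjusted levels are normal with SD s. The control tertile cuts are then at ±0.4307 SD. If cases excrete a fraction p less creatinine, their mean shifts up by d = −ln(1 − p) / s. Controls have equal thirds, so the null odds ratio is [1 − Φ(0.4307 − d)] / Φ(−0.4307 − d).
- p = 10%, s = 1.0: d = 0.105; 0.3725 / 0.2959 = 1.26. For s = 1.3 and 0.8 it is 1.19 and 1.33.
- p = 20%, s = 1.0: d = 0.223; 0.4178 / 0.2566 = 1.63. For s = 1.3 and 0.8 it is 1.46 and 1.84.

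The simulation agrees in direction and size. Residual log lean-mass differences of −0.05, −0.10 and −0.15 gave odds ratios of 1.11, 1.22 and 1.35, with 5%, 7% and 13% false positives.

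**The case against.** **Division is not stated.** The text speaks of adjusting and normalising, gives no formula and points to earlier reports. This stands as a limit. A ratio is still the natural reading: the section argues from creatinine concentration being inversely proportional to urine flow, and it applies the adjustment to the final concentrations, before any modelling.

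**The odds ratios are protected by design.** A reader might infer that creatinine adjustment biases the EDC odds ratios. The document does not support that. Controls are matched on age, BMI category and hospital, and step 3 shows no shift under age matching. BMI category is not lean mass, so a difference could remain, but nothing in the document shows that one exists or in which direction.

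**Estrogens.** A reader might extend the body-composition claim to them. The estrogen section does not make it, and no case-control comparison of estrogens is named. They are affected only because they receive the same kind of adjustment and enter the participant-characteristic models.

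**The models may contain age and body size.** A condensed article may leave the covariate list to the full plan, so its absence is no finding. Suitable covariates would remove much of the artefact. They would not make the stated property of the adjustment correct.

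**A ratio could be read as exposure per unit of muscle.** In that sense it does account for body composition, but only if EDC excretion rises in proportion to creatinine output. The document does not claim this.

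**The remedy does not reach muscle mass.** This stands. Muscle mass is not recorded, so a lean-mass difference at equal age, weight and height would remain after standardisation.

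**Conclusion.** The point holds in a limited form. The EDC section attributes to creatinine adjustment a property that conflicts with its own premise. If a ratio is used, it can create false associations of age and body size with adjusted EDC and estrogen levels in the planned participant-characteristic models. The size depends on how strongly creatinine output varies with age and muscle, which the document does not give. At an assumed fall of 0.5% to 1% per year, the ratio drifts 25% to 57% between ages 25 and 70, and the age test rejects in roughly 10% to 69% of null studies instead of 5%.

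The EDC odds ratios are largely protected by the matching. The values of 1.26 and 1.63 in step 4 show what a residual 10% or 20% deficit in cases would do at log SD 1.0. They are not estimates of bias in this study.

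**What to change.** 1. In the EDC section, delete body composition as something the adjustment accounts for, and state the formula by which creatinine enters.
2. Predict log creatinine from age, weight, height and race. Divide each EDC and estrogen concentration by the ratio of observed to predicted creatinine.
3. In the Statistical analysis section, include log creatinine, age and body size as covariates in the models that use these levels. Log creatinine alone is not enough (step 2 of the working).
4. Form the control-based EDC tertiles from the standardised values.
5. Report the simple creatinine ratio as a sensitivity analysis.
6. State as a limitation that muscle mass is not recorded and that a lean-mass difference at equal age, weight and height may remain.

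Cost: text changes in the two urine sections and the Statistical analysis section. Creatinine, age, weight, height and race are already collected, so no new samples or assays are needed. The standardised values are slightly less comparable with studies that use the simple ratio, which the sensitivity analysis covers.

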### Quantitation of urinary concentrations of the parent estrogens and estrogen metabolites

Concentrations of estrone, estradiol and 13 estrogen metabolites [2-hydroxylated estrogen metabolites (2-hydroxyestrone, 2-methoxyestrone, 2-hydroxyestradiol, 2-methoxyestradiol, and 2-hydroxyestrone-3-methyl ether); 4-hydroxylated estrogen metabolites (4-hydroxyestrone, 4-methoxyestrone, and 4-methoxyestradiol); and 16-hydroxylated estrogen metabolites (16α-hydroxyestrone, estriol, 17-epiestriol, 16-ketoestradiol, and 16-epiestriol)] will be determined in fasting spot urine samples, adjusting for urinary creatinine levels (mg/dL). The quantitation of urinary estrogens will be assessed by gas chromatography tandem mass spectrometry using a triple quadrupole analyzer as previously described with minor modifications [33, 34]. Briefly, one mL of urine with 25 μL of internal standards solution will be extracted using C18 SPE cartridge (Sep-Pack C18) previously conditioned with 4 mL of methanol and 4 mL of water. After loading the urine sample, the cartridge will be washed with 4 mL of water. The treated urine will then be evaporated. Three mL of acetate buffer 0.1 M (pH 4.5) and 3 μL of β-glucuronidase will be added to the treated urine after being evaporated, and the mixture will be incubated for 3 h at 55 °C. After cooling to room temperature, pH will be increased to approximately 9.5. Then, samples will be extracted with 6 mL of tert-butyl methyl ether by shaking in a rocking mixer and centrifuged. Finally, the organic layer will be evaporated to dryness under a stream of nitrogen. Two μL of the derivatized extract will be injected in split mode into the GC-MS/MS system. All hormone assessments will be carried out simultaneously to reduce intralaboratory variation.

